## Abstract

**Background:**

The UK Equality Act 2010 makes it unlawful for employers to ask health questions before making an offer of employment except in certain circumstances. While the majority of employers would prefer applicants to disclose a mental illness at the application stage, many people either wait until they have accepted the job and then disclose to an occupational health professional, or do not do so at all due to the anticipation of discrimination or a wish for privacy. However, non disclosure precludes the ability to request reasonable adjustments in the workplace or to make a claim of direct discrimination. Disclosure to employers is therefore a difficult decision. A recent pilot study by our group of the CORAL decision aid showed that it helped mental health service users clarify their needs and values regarding disclosure and led to reduction in decisional conflict. The present proof of concept trial aims to determine whether a full scale randomised controlled trial (RCT) is justifiable and feasible, and to optimise its design.

**Methods:**

In this single blind exploratory RCT in London, a total of 80 participants (inclusion criteria: age ≥18 years, on the caseload of a specialist employment adviser working with people with mental illness; referred to the adviser either from primary care via Improving Access to Psychological Therapies or secondary mental health service; currently seeking or interested in either paid or voluntary employment, and a Decisional Conflict Scale score of 37.5 or greater and stage of decision score 1–5) will be recruited from vocational advice services. After completing a baseline assessment, participants will be randomly assigned to one of two conditions (1) Use of the CORAL Decision Aid (DA) in addition to treatment as usual or (2) Treatment as usual. Those allocated to the DA condition will be given it to read and complete, and the researcher will be present to record the time taken and any content that causes confusion. Intervention participants may keep the decision aid but are discouraged from showing it to other service users to avoid contamination. Follow up interviews will be conducted at 3 months. Primary outcomes are: (i) stage of decision making score; (ii) decisional conflict scores and (iii) employment related outcomes. Secondary analyses will identify predictors of disclosure and qualitative analysis will explore the impact of the intervention.

**Discussion:**

A reduction in decisional conflict regarding disclosure leading to more effective job seeking activity could have significant economic consequences for people with mental illness in terms of employment rates and productivity.

**Trial registration number:**

NCT01379014 (ClinicalTrials.gov Identifier)

## Background

People with mental health problems frequently report discrimination in employment. In a US survey 61% (n = 1,301) felt they had been turned down for a job for which they are qualified when they disclosed their illness
[1]. In the UK, 56% (n = 411) believed that they had definitely or possibly been turned down for a job in the past because of their mental health problems
[2]. Similarly, in a recent international survey, 64% of participants (n = 736) reported stopping themselves from applying for work, training or education due to anticipated discrimination as a result of their diagnosis of schizophrenia
[3]. Anticipated discrimination by employers also forms a barrier to seeking mental health care; this obstacle was reported more frequently than any other in a recent study
[4].

Given these high frequencies of experienced and anticipated discrimination among people with mental health problems, many choose not to disclose their condition prior to being offered a job. This contrasts with employers’ reported preferences that they do so, for example 77% in a UK sample surveyed in 2009
[5]. However, with the introduction of the Equality Act 2010 it is now unlawful for employers in Britain to enquire about an applicant’s disability or health, until that person has either been offered a job or been included in a pool of candidates to be offered a job when a suitable position arises. Nothing in the Act prevents employers asking health related questions once recruitment decisions have been taken. This restriction is qualified by several exclusions and is only enforceable by the Equality and Human Rights Commission. However, its breach constitutes evidence of disability discrimination.

In some circumstances disclosure may be obligatory. For example, if a job environment is such that one’s disability could present a risk to one’s health and safety or that of colleagues
[6]. However, in most cases the Act does not obligate disclosure of a mental illness prior to employment, so it is up to the job candidate to decide whether to do so. There are two important legal considerations
[7]. First, a claim for direct discrimination or discrimination arising from disability can only be made where the employer knew or ought to have known that the person was disabled. Second, no duty arises to provide ‘reasonable adjustments’ if the employer does not know or could not reasonably be expected to know that a person has a disability. There are also many other considerations. Will colleagues misinterpret symptoms of mental illness
[8] e.g. as substance misuse if one does not disclose? Will they gossip
[9], ignore them
[8] or interpret every expression of emotion as a symptom if they do? How much should one say, when and to whom? Disclosure of mental illness in the employment context is therefore a personal, multilayered and potentially difficult decision.

A decision aid (DA) is an educational intervention designed to help an individual make a specific and deliberate choice between two or more options. They are commonly used in medical decision-making when individuals need to choose between treatment or screening options
[10]. A systematic review of 17 randomised trials of DAs found that, compared with controls, DAs produced higher knowledge, more active participation in decision making and lower levels of decisional conflict
[11,12].

This suggests that a DA may be a useful intervention to increase knowledge about disclosure, reduce decisional conflict or increase active participation in this employment decision making.

We have recently developed a DA to assist people with mental health problems consider disclosure in the employment context (Conceal Or ReveAL, or CORAL). In a non-randomised pilot study
[13], the CORAL DA demonstrated preliminary evidence of acceptability, feasibility and effectiveness in a group of 15 service users. We now wish to determine through a randomised controlled trial whether using the CORAL DA changes the user’s behaviour with respect to seeking or retaining employment in ways that result in higher levels of employment and greater use of workplace accommodations. These outcomes require larger sample sizes and a longer follow up period than are justifiable at this point. To determine whether such a trial is justifiable and feasible and to optimise its design, our next step is to conduct a proof of concept RCT.

## Methods

### Design

The CORAL trial is an individual-level single-blind RCT of the CORAL decision aid compared with a treatment as usual control for people receiving primary (Improving Access to Psychological Therapies (IAPT)) or secondary mental health care services in south east London. The total duration of the study will be two years, to allow for: regulatory approvals, recruitment; provision of the intervention; follow-up assessments; qualitative exploration of use of the DA; and data analysis, using intention to treat methods. Recruitment to the trial began in July 2011 and is due for completion in June 2012. Follow-up assessments began in October 2011 and will be completed by September 2012.

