### Objectives

The aims are to determine whether a full scale RCT of the CORAL decision aid tool is justifiable and feasible and to optimise its design
[15,16]. Specific objectives are to (i) establish parameters of a future trial, by examining the effect of the DA on decisional conflict regarding disclosure both immediately and at 3 months post first use and determining the optimal primary outcome for a full scale trial from a range of employment related measures; (ii) optimise the evaluation, by testing study procedures, including: the sample that can be recruited and retained using the inclusion and exclusion criteria; the resource implications in terms of full time equivalent needed for research assistants to recruit sufficient numbers and carry out the study procedures in the time available; whether the batch of measures is acceptable vs. leads to too much respondent burden; the use of a questionnaire on employment and disclosure related activities; the randomisation method, in this case individual level randomisation, including the methods for avoiding and measuring contamination; recruitment and retention methods for service users and vocational counsellors; the choice of measures for a full scale trial based on results of qualitative interviews with participants; (iii) optimise the intervention, by collecting feedback on the DA form a larger sample than was used in the previous pilot.

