### Hypotheses

While we shall conduct hypothesis testing this is not the main objective of the study, as this is the purpose of the future large scale trial. The reporting of this study will not therefore emphasize the results of hypothesis testing over the reporting of whether the objectives were met
[17]. Our hypotheses are derived from the conceptual model in Figure
2 and fall into three groups. Regarding the effect of the intervention, we expect that, regardless of what the disclosure decision is, having a lower level of decisional conflict and being at a later stage of decision will allow the participant to take action regarding seeking work, resulting in a greater level of empowerment and a reduction in behavioural withdrawal. Thus, compared to the control group, those in the intervention group will show at 3 months
[1]: lower decisional conflict regarding disclosure
[2]; a later stage of decision making regarding disclosure
[3]; higher frequencies of work related actions
[4]; a higher level of empowerment
[5] lower frequencies of withdrawal as a response to stigma (in any context rather than just employment). The model shown in Figure
2 will be investigated using process evaluation and qualitative data collection to identify the most robust associations to carry forward into a final modified and simplified version of the model to be used in the subsequent full scale RCT. 

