### Sample size

The heuristic sample size for pilot studies is 30 per group
[16]. However, we have elected to use a larger sample size so that we can test the effect of the DA with respect to a meaningful reduction in decisional conflict. The pre-post difference detected on the Decisional Conflict Scale in a preliminary study
[13] was found to be 16.5 points in the intervention group, with a standard deviation of 17.5. Estimating the effect of treatment as usual (i.e. vocational advisor standard support) at 4 points, this gives a standardised effect size of 0.71. Group sizes of 32 at the follow-up are needed to have 80% power to detect a difference of this size or greater at the 5% significance level. Further to test our exploratory hypotheses and refine our conceptual model, increasing from 64 (2×32) to 70 participants at follow up will allow logistic regression analysis to study relationships between baseline predictors and disclosure using 6 variables (plus the group variable), using the minimum of 10 per variable. Since we anticipate some loss to follow up at 3 months we shall aim to recruit 40 per group i.e. a total of 80 participants. Qualitative interview sample sizes are based on our expectations for the number of interviews required to cover a range of experiences and to reach the point where no new themes are identified in the analysis.

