### Analysis plan

The principal analysis of effectiveness will compare the primary and secondary outcome measures at 3 months. Changes in Decisional Conflict Scale scores are not prone to cut-off limits and are expected to be normally distributed. For both this and other normally distributed continuous outcome measures, an independent two sample t-test will be used to compare the change in effects (T1-T0) for the two groups (control and intervention). When continuous variables are predicted to be skewed (e.g. number of disclosures made), these can be tested using a two-sample Wilcoxon rank-sum test. The differences in number of disclosures made (T1-T0) for the two groups (control and intervention) can be compared. While items such as job offers and disclosure will be too infrequent to provide reliable comparisons, others such as appointments kept with the vocational adviser and submitted applications will be used as proxy measures for future employment outcomes. We will use confidence intervals for the effect sizes for these employment related activities to judge whether a full scale trial is indicated.

Attendance and dropout rates can be compared in terms of their baseline characteristics to see whether there are any obvious differences between retained and dropout participants. Adjustments to these analyses will be made to compensate for multiple testing. To study factors predicted by our model (see Figure
2) to be associated with disclosure we will use logistic regression. Each instrument will be studied to see whether it performs well enough for inclusion in a future trial. A correlation matrix will be formed from the items to calculate internal consistency and reliability, and to assess the appropriateness of forming composite or summary scores for previously defined sub-scales. Along with the histograms of each subscale, the data allow assessment of the appropriateness (particularly ceiling and floor effects) of the measures. Variables that perform well (and that appear not to be measuring the same thing) will be included in the logistic regression model, while adjusting for gender and diagnosis as these have been found to be associated with disclosure in other studies
[28,29].

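### The stated t-test on change does not deliver the intention-to-treat label, and one objective times follow-up from an event that controls never have

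*Protocol article*

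**What the plan says.** The Design section commits to "data analysis, using intention to treat methods". The Analysis plan then names the test for the Decisional Conflict Scale and other normally distributed measures: "an independent two sample t-test will be used to compare the change in effects (T1-T0) for the two groups". The Sample size section counts participants present at follow-up. It needs 32 per group for power, raises the follow-up total from 64 to 70 for the logistic regression, and recruits 80: "Since we anticipate some loss to follow up at 3 months". For dropouts, the Analysis plan gives a comparison of baseline characteristics with retained participants. Under Sequence generation, randomisation is stratified by referral source and by time out of work; the stated t-test uses neither.

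On timing, objective (i) asks for the effect on decisional conflict "both immediately and at 3 months post first use". Elsewhere there is no such anchor. The Abstract says "Follow up interviews will be conducted at 3 months", the Hypotheses say "those in the intervention group will show at 3 months", and the Analysis plan says "The principal analysis of effectiveness will compare the primary and secondary outcome measures at 3 months".

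**The concern.** Two statements do not fit together.

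- **Label and test.** Intention to treat concerns everyone randomised, in the arm to which they were allocated. A change score does not exist for a participant with no 3-month value, so the test as written analyses those who were followed up.
- **Time origin.** A randomised comparison needs an origin that is defined in the same way in both arms. First use of the aid has no counterpart under usual care, nor for an intervention participant who never uses it. If objective (i) were applied literally, the interval from baseline to T1 could differ between arms, and a non-user would have no due date for follow-up.

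At stake is the decisional conflict effect, which objective (i) lists among the parameters for a future trial. The choice of test also affects precision in a study of this size.

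**Working it through.** **1. The article's own figure.** Inputs from Sample size: intervention change 16.5, usual-care change 4, SD 17.5. The difference is 16.5 − 4 = 12.5, and 12.5/17.5 = 0.71. At two-sided 5% and 80% power, the normal approximation gives 31 per group and the exact t-test 31.8, so 32. Power at 32 per group is 80.3%. The stated 32 reproduces, and it counts people at follow-up.

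**2. Implied loss.** No rate is stated. From 80 to 70 is 1 − 70/80 = 12.5%. From 80 to 64 is 1 − 64/80 = 20%. So 10 to 16 randomised participants would have no T1.

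**3. What missing T1 could do.** Take the same fraction m lost in each arm and 12.5 as the completer difference. The outcomes of those lost are assumptions, since the article gives none.

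If lost intervention participants change by x and lost controls change as observed controls do, the difference in all randomised is 16.5(1 − m) + xm − 4. If instead lost controls change by y and the intervention arm is unaffected, it is 16.5 − [4(1 − m) + ym].

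| Assumption about those lost | m = 0.125 | m = 0.20 |
|---|---|---|
| Intervention, x = 0 | 10.4 | 9.2 |
| Intervention, x = 4 (as usual care) | 10.9 | 10.0 |
| Intervention, x = 16.5 (as observed intervention) | 12.5 | 12.5 |
| Controls, y = 0 | 13.0 | 13.3 |

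In the x = 4 row the completer figure is too high by 12.5/10.94 = 1.14 to 12.5/10.0 = 1.25, that is 14% to 25%. In the last row it is too low. Imputing within arm reproduces the x = 16.5 row, so on its own it would not address the x = 4 scenario.

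**4. Time origin.** Objective (i) counts from first use; the Abstract, Hypotheses and Analysis plan give no origin. The Design section reports "Recruitment to the trial began in July 2011 and is due for completion in June 2012", with follow-up from October 2011 to September 2012. Both ends are shifted by three months, which fits timing from recruitment. The article gives no interval between randomisation and the meeting at which the aid is handed over, so I put no size on this part.

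**5. Precision of the test.** With pre-post correlation ρ and equal variances σ² (both assumed), the change score has variance 2σ²(1 − ρ) and the baseline-adjusted score σ²(1 − ρ²). The ratio is (1 + ρ)/2.

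- ρ = 0.3: 0.65, so the variance falls by 35%.
- ρ = 0.7: 0.85, so the variance falls by 15%.

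Reading 17.5 as the SD of change, with 35 per arm, the change-score standard error is 17.5 × √(2/35) = 4.18. The 95% half-width is about 1.96 × 4.18 = 8.2 points. Adjustment gives 8.2 × √0.65 = 6.6 to 8.2 × √0.85 = 7.6 points.

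**The case against.** The strongest reply is that a condensed article need not set out missing-data methods. Naming a t-test on change does not forbid imputing T1, and a statistical analysis plan that is not shown may do so. That stands: the lack of a missing-data rule is not an error here. What remains is that the published test, with a sample size that counts those at follow-up, does not by itself carry the label.

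A reader might infer that the trial analyses only users of the aid. The documents do not support this. The Analysis plan compares the allocated groups, no section removes non-users, a researcher is to meet every intervention participant to hand over the aid, and the calendar fits timing from recruitment. The first-use wording occurs in one objective only.

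A reader might also infer that the test favours the aid. That is one possibility among several, as the table shows. The 20% loss is also the less likely end, because the article itself raises the follow-up target from 64 to 70.

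Needing T0 costs little, since baseline is completed before randomisation and the Decisional Conflict score is an entry criterion.

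Finally, the article plays down hypothesis testing and judges the case for a full trial from confidence intervals for employment-related activities. This limits the consequence of a biased decisional conflict effect but does not remove it, because objective (i) still asks for that effect.

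**Conclusion.** The point holds in a limited form. The intention-to-treat statement and the stated test do not match for the 10 to 16 of 80 participants expected to lack T1, and objective (i) uses a time origin that is undefined in one arm.

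The effect on the estimate is uncertain in direction: 9.2 to 13.3 points in all randomised against 12.5 in completers, depending wholly on assumed outcomes for those lost. The usual-care assumption gives 10.9 to 10.0.

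The clearer gain is in the analysis itself. Adjusting for baseline would cut the variance of the effect by about 35% to 15% relative to the change score if the pre-post correlation is 0.3 to 0.7 and the variances are equal. It would also take account of the stratified randomisation, which the t-test does not.

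**What to change.** - **Time origin.** Reconcile objective (i) with the other sections by counting 3 months from randomisation in both arms. State that intervention participants stay in follow-up and analysis whether or not they used the aid.
- **Test.** Replace the change-score t-test for decisional conflict with a regression of the 3-month score on arm, baseline score, referral source and time out of work.
- **Label and sensitivity.** Describe the result as analysis by allocated group among those with a 3-month score. Add one sensitivity analysis in which missing intervention participants take the usual-care change.

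**Cost.** Wording and modest programming. The baseline score and both strata are already collected. Follow-up began in October 2011, so interviews already held cannot be moved, but the reported calendar suggests that few would need to be. The sensitivity result may be less favourable to the aid.

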### Setting

The settings are in London at locations where vocational advisers employed or contracted by an NHS Foundation Trust work with clients from the Trust and from IAPT.

### Participants

Eligible service users will (i) be on the caseload of a specialist employment adviser working with people with mental illness; (ii) have been referred to the adviser either from the primary care based mental health service Improving Access to Psychological Therapies (IAPT) or secondary mental health care service; (iii) be aged 18 years or older; (iv) be currently seeking either paid or voluntary employment or interested in seeking paid or voluntary employment (v) have a Decisional Conflict Scale score of 37.5 or greater (showing at least moderate decisional conflict) and a Stage of Decision Scale score of 1–5 (showing the decision has not yet been reached); and (vi) give written, informed consent. We will exclude service users who have insufficient literacy in English to use the DA or who lack capacity to provide informed consent. Figure
1 shows the CONSORT flow chart for participants.

**Figure 1 F1:**
[figure not shown]
Consort flow chart of CORAL trial design.

### Intervention

A researcher will meet with each participant in the intervention group and give them the DA to read and complete.

The DA has been designed for use independent from or as an adjunct to a clinical encounter
[14]. It includes six sections
[1]: the pros and cons of disclosure
[2]; personal disclosure needs
[3]. personal disclosure values
[4]; when to tell
[5]; whom to tell
[6]; making a decision, which summarises the previous sections and asks the participant to reflect on responses and make a decision regarding when, what and to whom to disclose. The researcher’s main role will be to record the time taken to read and complete the DA and answer any questions or clarify areas of confusion which arise. If the participant has difficulty in understanding the DA then it will be explained that part of the purpose of the study is to test how easy it is for people to complete the DA and they should use their best guess to answer the questions in it. They will be reminded that there is a chance to discuss any areas which caused confusion at a later stage of the interview. If the participant is not satisfied with this explanation then a choice of what the statement could mean will be given. If this is not sufficient then a more prescriptive set of instructions will be provided, with the researcher guiding the participant through the DA as an interview if necessary. Following this meeting, the participant will be given their DA to keep and continue to receive standard support from the vocational advisers, as per the control condition.

